### Sample size {14}

For statistical analyses of the primary and secondary outcomes, 2-factorial repeated measures ANOVAs are planned (see {20a}). A power analysis for this statistical procedure has been conducted for sample size estimation (GPower 3.1.9.2). Due to the heterogeneity of older persons, the effect size (ES) in this study is estimated to be small to moderate (*f* = .3). With an *α* = .05 and power 1 − *β* = .80, the estimated sample size needed for this effect size is approximately *N* = 111 for a between-group comparison between IG and CG with a 1:1 allocation and three measurement time points. Based on an estimated drop-out rate of 20%, a sample size of *N* = 140 will be adequate for the main objective of this study and should allow for the expected drop-out rate.

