## Assignment of interventions: allocation

### Sequence generation {16a}

A statistician, who was otherwise not involved in the planning of the study design, generated computer-based randomization lists. The criteria for randomization of participants to IG or CG are gender and bicycle type (e-bikes/unmotorized bicycle), whereas couples are block-wise randomized to ensure the participation together in one group.

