## Statistical methods

### Statistical methods for primary and secondary outcomes {20a}

Data analysis will be performed using descriptive statistical analysis and inferential statistics. The sample data will be presented by frequencies or percentages, means ± standard deviation or median and interquartile range, and graphics. The IBM® SPSS® Statistics for Windows, version 26 software (IBM Corp., Armonk, NY, USA) will be used for all statistical analyses.

For the evaluation of primary outcomes, 3 × 2 analyses of variance for repeated measurements (ANOVA) will be used: For evaluating the long-term changes in CRP and cortisol (hair and saliva), 2-factorial ANOVAs with the factors “time point” (T0, T1, T2) and “group” (IG or CG) will be conducted. For the evaluation of the acute effects of the training intervention, further ANOVAs with the factors “time point” (before, after, and 20 min after the training) and “training number” (second or seventh training) will be calculated. For the evaluation of further secondary outcomes, comparable analyses will be conducted.

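### Couples are allocated to one arm as a unit, but the between-arm ANOVA and the sample size treat all participants as independent; if partners' changes correlate positively, standard errors are somewhat too small

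*Protocol article*

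**What the plan says.** Three sections of the protocol article bear on this.

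- **Sequence generation {16a}.** "The criteria for randomization of participants to IG or CG are gender and bicycle type", and "couples are block-wise randomized to ensure the participation together in one group". For a couple, the unit that is allocated is therefore the pair.
- **Statistical methods {20a}.** For long-term changes in cortisol and CRP, "2-factorial ANOVAs with the factors “time point” (T0, T1, T2) and “group” (IG or CG) will be conducted". No term for couple appears, and no other allowance for pairs is made.
- **Sample size {14}.** The calculation is made for the same procedure ("2-factorial repeated measures ANOVAs are planned"), with f = .3, α = .05 and power .80. It gives about 111 participants "for a between-group comparison between IG and CG with a 1:1 allocation and three measurement time points", raised to 140 for 20% drop-out. No design effect is mentioned.

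Nothing elsewhere changes this. Additional analyses {20b} are given as not applicable, and {20c} deals with adherence only. Outcomes {12} defines the primary outcome as the change in cortisol from T0 to T1.

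**The concern.** A repeated-measures ANOVA allows for correlation between the measurements of one person but takes different persons as independent. The allocation rule creates pairs of people who are always in the same arm. If the two partners tend to change in the same direction, a pair carries less information about the group difference than two unrelated participants do, and the ANOVA counts it as two.

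The group-by-time test would then reject too often under the null hypothesis, its confidence interval would be too narrow, and the 111 evaluable participants would give less than the intended power. There is almost no reserve, because the calculation sits just above 80%.

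This is not a detail left to an analysis plan. The article itself states the allocation unit, the ANOVA factors and the procedure behind the sample size, and they do not fit together.

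**Working it through.** **Inputs from the article.** f = .3, α = .05, power .80, two arms at 1:1, three time points, N = 111 evaluable, 20% drop-out, N = 140 (all from {14}); couples kept in one arm ({16a}).

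**Inputs that the article does not give.** The share c of analysed participants who belong to a couple, and the within-couple correlation (ICC) of the outcome change. Both are assumed over a range.

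**Step 1: reproduce the plan's figure.** For the multivariate group-by-time test, the noncentrality is λ = f² × N with 2 and N − 3 degrees of freedom. At N = 111, λ = 0.09 × 111 = 9.99, and power with 2 and 108 degrees of freedom is 0.803. This matches the stated figure. The formula counts every participant as independent. Drop-out: 111 / 0.80 = 138.75, so 139, which the plan rounds to 140. Conversely, 140 × 0.80 = 112 evaluable, with power 0.807 under independence.

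**Step 2: design effect.** In an arm of n participants, c × n of them each have one partner in the same arm. The variance of the arm mean is therefore (σ²/n) × (1 + c × ICC), and DE = 1 + c × ICC. With pairs it cannot exceed 1 + ICC.

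**Step 3: consequences.** The true standard error is √DE times the one that ignores couples. For a nominal 5% test on one degree of freedom, the actual type I error is 2 × [1 − Φ(1.96/√DE)]. Effective N is 112/DE, and power is recomputed with λ = 0.09 × 112/DE and 2 and 109 degrees of freedom.

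| c | ICC | DE | √DE | Type I error, formula | Type I error, simulated | Effective N | Power |
|---|---|---|---|---|---|---|---|
| 0 | – | 1.00 | 1.000 | 0.050 | 0.050 | 112 | 0.807 |
| .2 | .1 | 1.02 | 1.010 | 0.052 | 0.053 | 109.8 | 0.799 |
| .3 | .3 | 1.09 | 1.044 | 0.061 | 0.059 | 102.8 | 0.770 |
| .5 | .5 | 1.25 | 1.118 | 0.080 | 0.079 | 89.6 | 0.709 |

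The simulation used a t test on change scores with 112 participants, whole couples in one arm, and 40,000 runs per row. For the two-degree-of-freedom test over all three time points, the formula gives slightly more: 0.053, 0.064 and 0.091 in the last three rows.

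**The case against.** The strongest reply is that the consequence is conditional and may be small. Several parts of it stand.

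- **No correlation is documented.** A reader might infer that partners' values are correlated and that type I error therefore exceeds 5%. The article gives no within-couple correlation, so this does not follow.
- **Correlation in levels is not the relevant quantity.** A shared household and routine make cortisol levels similar. The primary outcome is a change, and stable shared influences largely cancel in it. Only shared change matters, so a low ICC is quite possible.
- **Intact pairs may be few.** Each person must qualify individually ({10}) and consent to each specimen type ({26b}). Exclusion of the non-adherent ({20c}), exclusion of glucocorticoid users and unobtainable hair (Potential risks and limitations) can break pairs before analysis. The article does not support assuming that a majority of participants are in couples.
- **An opposing effect exists.** Allocation is stratified by gender and bicycle type, and {20a} adjusts for neither. If these factors predict the change, the unadjusted standard errors are conservative, which would offset some or all of the inflation.
- **Course groups.** A reader might also infer further clustering from the shared lessons and lectures. The article gives no group size and no correlation for them, so no figure can be attached, and none is claimed here.

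What the reply does not remove is the mismatch itself: pairs are allocated together by rule, and neither the stated model nor the stated sample size allows for them.

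**Conclusion.** The point holds in conditional form. The mismatch between allocation and analysis is certain from the text; its effect is not. If partners' T0–T1 changes are positively correlated, the between-group standard errors are too small by a factor √DE. With few couples and a low correlation this is trivial (1%, type I error about 5.2%). At share .3 and ICC .3, type I error is about 6% and power about 0.77. At share .5 and ICC .5, they are about 8% and 0.71. Share and ICC are assumptions in every case.

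The point covers the IG-versus-CG comparisons. It does not carry over in the same way to the second-versus-seventh-lesson analysis, which lies within the intervention group. The change is worth making because it is cheap and protects the primary test if couples turn out to be common, not because the planned result is shown to be invalid.

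**What to change.** **In {20a}**, analyse the T0–T1 change, or the T1 value adjusted for T0, with a random effect for couple and single participants as clusters of one. Standard errors clustered on couple are an alternative. If a model of all three time points is kept, include a couple-by-time effect or cluster on couple. A couple random intercept alone is not enough there: it absorbs the level that partners share but not the change that they share, and the change is what the group-by-time contrast tests.

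**In {14}**, give the expected share of participants in couples and an assumed ICC, and state power on the effective N (evaluable N divided by 1 + share × ICC). This need not raise enrolment.

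**Cost.** Couples must be identified in order to be allocated together, so the only data step is to carry a couple identifier into the analysis file. Intervals become slightly wider and the stated power slightly lower. If couples prove few, the results will hardly differ from those of the planned ANOVA.

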### Concealment mechanism {16b}

The recruiting team has no access to the randomization list, and the randomizing person receives only the stratification information to assign the intervention.

### Implementation {16c}

After the assignment of the informed consent and the baseline assessments by trained study staff, randomization is performed by enrolling participants in concealed randomization lists by a separate person that only receives the information necessary for stratification.

## Assignment of interventions: blinding

### Who will be blinded {17a}

All biological specimens are labeled by a participant code only, which allows blinding during laboratory analysis.

### Procedure for unblinding if needed {17b}

Not applicable

## Data collection and management

### Plans for assessment and collection of outcomes {18a}

After completion of data collection for each time point, data entry will be performed contemporary to ensure identification of missing data and any discrepancies. This enables to record missing data or wrong inputs from participants. All data will be cleaned, inspected for outliers, and tested for normality of distribution prior to hypothesis testing. Composite scores, e.g., for questionnaires, will be computed where appropriate. Quality control for laboratory data is performed first by using standard procedures and second including intra- and inter-assay variability. Laboratory values not complying with quality control requirements will be repeated. The means and standard deviations for all variables will be computed, and preliminary analyses testing for age and gender effects will be performed.

### Plans to promote participant retention and complete follow-up {18b}

Participants receive reminder calls and invitations to appointments to promote participants completing the intervention and follow-up assessments. Furthermore, each participant receives own data at the end of the study.

### Data management {19}

In general, we will follow the data policy by FAU, released December 2019, regulating data management. All data will be handled adhering to the current German and European data protection laws. Ethics approval has been obtained by the Ethics Committee of Friedrich-Alexander-Universität Erlangen-Nürnberg, Germany, #22_20B, June 22, 2020, and all data collection, storage, and protection procedures were evaluated by the local data protection authority (“Datenschutzbeauftragter der FAU”). All data will be pseudonymized, i.e., a numerical code will be generated and used as a data identifier. Participants will be granted the right to ask for their data to be deleted as long as data is not completely anonymized. One year after the completion of data analyses, all personal information will be destroyed. De-identified data will be stored on secure file servers for 10 years according to DFG recommendations. Data entry will be double-checked by a trained study nurse of the IBA to guarantee correctness, completeness, and plausibility of the provided information.

### Confidentiality {27}

Personal information will be stored in a password-protected data file, separate from all other data.

### Plans for collection, laboratory evaluation, and storage of biological specimens for genetic or molecular analysis in this trial/future use {33}

All biological specimens will be collected at the IBA and stored at room temperature (HCC) or at − 30 °C (saliva and blood samples) as described above. After completion of sample collection for one time point, laboratory analysis will be conducted at the laboratories of the IBA and the Chair of Health Psychology. All samples will be stored until the end of the study for potential re-analyses.

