### Objectives {7}

The aim of the study is to investigate the acute and chronic physiological stress-related health benefits of a cycling intervention in older adults. The analysis of the patho-physiological parameters involves two parts: first, the effects of an 8-week cycling exercise training program on general cortisol and CRP levels and, second, the investigation of the acute physiological effects of a cycling training on cortisol and sAA as stress-related health outcomes. We hypothesize that the cycling intervention will have stress-reducing and health benefits in the long term. Furthermore, we hypothesize that the acute cycling training will be a physical stressor, which will be perceived as a stressor associated with anxiety (leading to HPA axis responses) at the beginning of the training. We expect that at the end of the intervention, the training will be a physical stressor only. This reduced acute stress should lead to a general reduction of cortisol levels.

Therefore, as a primary outcome, the following hypotheses will be tested:
Cortisol (measured in the saliva at bedtime and in the hair) will decrease significantly after the intervention in comparison with the control group.

Our secondary hypothesis is that the acute effects of a cycling training on salivary cortisol levels (as a marker for HPA axis activity) will be compared between the beginning and the end of the intervention and will be lower after the seventh than after the second lesson.

Furthermore, we will explore the following parameters to understand better the psychological adaptations to the cycling training: changes in fear of falling and perceived stress before and after the intervention. Moreover, the acute effects of the training on salivary alpha amylase, perceived stress, and anxiety will be investigated.

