## Methods: participants, interventions, and outcomes

### Study setting {9}

SiFAr-Stress is a controlled prospective study with parallel groups. The randomization of participants to an intervention (IG) or a control group (CG) will be stratified. The target populations of this study are community-dwelling older adults who are 65 years and older, who are living in the region of Nuremberg, Bavaria, Germany, and who participate in the SiFAr study. The participants of the main SiFAr study (Siebentritt H, Keppner V, [name], [name], Rappl A, [name], et al. Safer cycling in older age (SiFAr): a protocol of a randomized controlled trial. BMC Geriatr. 2021. submitted) will be identified by advertising the study in the local media (e.g., radio, newspaper, brochures) and by using a database of the study center. In addition, flyers will be displayed to specifically address potential participants. All participants of the main study will be offered to additionally participate in the sub-study. Participants additionally consent to give capillary blood, hair, and/or saliva samples. The study protocol was approved by the local ethics committee of the Friedrich-Alexander-Universität Erlangen-Nürnberg (number 22_20B). At the Institute of Biomedical Aging (IBA), participants take part in the assessment including questionnaires as well as functional and cognitive tests and capillary blood, hair samples, and saliva samples. All biological specimen analyses will be performed in the laboratory of the Chair of Health Psychology, Friedrich-Alexander-Universität Erlangen-Nürnberg. The study will be conducted in accordance with the Helsinki Declaration.

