#### Intervention description {11a}

SiFAr-Stress is an additional part of the SiFAr study following the time course of the main study. SiFAr consists of a practical and a theoretical part within 2 years. In the first year, the IG will participate in the multicomponent exercise program including cycling with a duration of 3 months, whereas the CG will take part in the theoretical course concerning bicycle-relevant lectures. Participants will be recruited from March to July. Both groups (IG + CG) will be tested for the performance in the cycling course and for functional and psychological parameters at T0 (before the intervention), T1 (after the 3-month intervention), and at 6 to 9-month follow-up (T2). To analyze stress- and health-related physiological parameters, biological specimen saliva, hair, and capillary blood will be collected. These patho-biological specimens will be collected during the intervention period to compare the change of different parameters during the intervention. The time points for biological specimen collection are identical as for functional and psychological parameters at T0, T1, and T2. The change of the concentration of stress hormone cortisol in the saliva specimen will be measured at T0 and T1. After completion of the intervention, all participants will be observed and tested as follow-up after 6 to 9 months.

Furthermore, short-term changes of cortisol concentration in the saliva specimens will be monitored for an acute-phase situation (prior, immediately after, and 20 min after the training session). The acute-phase situation will be determined twice during the training period, at the second and the second last training lesson. Therefore, the influence of the exercise training on the acute cortisol response in saliva will be determined.

In addition, hair specimens will be analyzed compared to longitudinal cortisol concentration. The inflammatory marker CRP will be analyzed in the capillary blood. The change in CRP concentration in the blood allows conclusions on inflammatory processes in the body.

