On the second and seventh training lessons (tr2 and tr7), participants will provide three saliva samples at three time points (before the training, immediately after the training, and 20 min after the training). Furthermore, perceived stress and anxiety will be rated on 10-point Likert scales, which have been used in previous research at the Chair of Health Psychology [45–48]. From the saliva samples, sAA and cortisol will be assessed as measures for SNS and HPA axis activity. The concentration of sAA will be measured with an enzyme kinetic assay, as previously described [41, 49], and salivary cortisol using a high-sensitive ELISA provided by IBL International according to the manufacturers’ instructions.

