### Outcomes {12}

The primary outcome is the change in cortisol and between the beginning of the intervention (T0) and after the intervention (T1). As secondary outcomes, the mean changes in fear of falling (FES-I) and psychological parameters (sAA, CRP, stress (PSS)) over a period of 3 months (after the intervention) and after a follow-up period of 6 to 9 months will be analyzed. Furthermore, the acute effects on cortisol levels during a session at the beginning and at the end of the training intervention (Tr1 and Tr7) will be assessed.

Cycling accidents during the intervention period present a potential risk for the participants and therefore might be a potential harm outcome.

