***Biological specimen***					
***Saliva samples***	X	3*x*^1^	3*x*^1^	X	X
***CRP (capillary blood sample)***	X			X	X
***Hair sample***	X			X	X

*MoCA* Montreal-Cognitive Assessment, *TMT* Trail Making Test, *SPPB* Short Physical Performance Battery, *VAS* visual analog scale, *FES-I* Falls Efficacy Scale-International Version, *CRP* C-reactive protein

^1^Saliva samples only for intervention group

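### Assaying saliva time point by time point, with no control arm at lessons 2 and 7, leaves a comparison of cortisol levels between the lessons open to between-run shift; the reactivity contrast is largely protected

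*Protocol article*

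**What the plan says.** All references are to the protocol article.

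- **Assay schedule, {33}:** "After completion of sample collection for one time point, laboratory analysis will be conducted". The section names two laboratories and keeps all samples to the end of the study in case they need re-analysis.
- **Time points, Table 2 in {13}:** the time-point row reads T0, tr2, tr7, T1, T2. The footnote to the tr2 and tr7 saliva entries reads "Saliva samples only for intervention group".
- **Sampling, Stress system activity:** at lessons 2 and 7, "participants will provide three saliva samples at three time points" (before, immediately after and 20 minutes after training).
- **Secondary hypothesis, {7}:** the acute effects on salivary cortisol levels "will be lower after the seventh than after the second lesson".
- **Analysis, {20a}:** ANOVAs with two factors, sample time within the lesson and training number; the sentence ends "second or seventh training) will be calculated". There is no group factor, and no term is named as the test of the hypothesis.
- **Stated purpose, {11a}:** "the influence of the exercise training on the acute cortisol response in saliva will be determined".
- **Outcome definition, {12}:** acute cortisol effects "at the beginning and at the end of the training intervention (Tr1 and Tr7".
- **Laboratory, {9}:** "All biological specimen analyses will be performed in the laboratory of the Chair of Health Psychology".
- **Quality control, {18a}:** laboratory control covers intra- and inter-assay variability, and failing values are repeated. No limits are given.

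**The concern.** If all lesson-2 samples are assayed in one period and all lesson-7 samples in a later one, any net calibration shift between the two adds to the difference between lessons. At T0, T1 and T2 a shift common to both arms drops out of the comparison of arms. At tr2 and tr7 only the intervention group is sampled, so nothing absorbs it.

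Whether this matters depends on the ANOVA term that is read as the answer. The wording in {7} fits a comparison of cortisol levels after the two lessons (the training-number main effect). It also fits a comparison of the within-lesson response (the interaction of sample time with training number). A shift feeds straight into the first and hardly into the second. On the levels reading, a downward shift at lesson 7 could produce the predicted result and an upward shift could hide it.

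Apart from any drift, a change within one arm cannot by itself establish the influence of the training as {11a} puts it. Habituation to sampling, season and differences between sessions remain as other explanations.

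**Working it through.** **1. The plan's own figures.** The sample size in {14} concerns the comparison of arms over T0, T1 and T2, not the lessons. It reproduces: f = 0.3, α = 0.05, numerator df 2, denominator df N − 3, λ = 0.3² × 111 = 9.99 gives power 0.8035 at N = 111. Drop-out: 111/0.8 = 138.75, so 139, close to the stated 140. The figure carried forward is 140 × 0.8 = 112 completers, or 56 in the intervention group.

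**2. Does assay run follow lesson?** {33} ties analysis to completion of one time point, and Table 2 makes tr2 and tr7 two time points. Read together, the lessons are assayed separately. {33} does not say so outright, so this is the natural reading and not a stated fact.

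**3. Level comparison (training-number main effect).** Assumptions: n = 56; SD of the paired log difference 0.4 or 0.6; no true change; net proportional shift s between lessons.

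z = ln(1 + s) / (SD/√56); false-positive rate = P(|Z + z| > 1.96).

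SD/√56 = 0.0802 for SD 0.6 and 0.0535 for SD 0.4.

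| Shift s | ln(1 + s) | z (SD 0.6) | Rate | z (SD 0.4) | Rate |
|---|---|---|---|---|---|
| 5% | 0.0488 | 0.61 | 9% | 0.91 | 15% |
| 10% | 0.0953 | 1.19 | 22% | 1.78 | 43% |
| 15% | 0.1398 | 1.74 | 41% | 2.61 | 74% |

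**4. Independent check and the interaction.** A simulation (4,000 runs per setting) used 56 participants, typical values of 4.0, 5.0 and 5.5 nmol/L at both lessons, between-person log SD 0.4, and session and residual log SD 0.25 each. These values are also assumed. They imply an SD of the paired log difference of √[2 × (0.25² + 0.25²/3)] = 0.41, close to the lower SD above.

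| Shift at lesson 7 | Scale | Main effect falsely significant | Interaction falsely significant |
|---|---|---|---|
| none | raw | 5% | 5% |
| −0.5 nmol/L | raw | 32% | 4% |
| −5% | raw | 14% | 5% |
| −10% | raw | 41% | 6% |
| −15% | raw | 76% | 8% |
| −20% | raw | 94% | 11% |
| −15% | log | 83% | 5% |
| −0.5 nmol/L | log | 60% | 9% |

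The algebra explains the pattern. If a lesson-7 value is read as a + (1 + s)X, the rise from the first to the third sample is read as (1 + s)(X₃ − X₁). The additive part a cancels and s only rescales the rise. On the log scale with a = 0, ln(1 + s) cancels exactly. With s = −10% the simulated raw rise is understated by about 0.17 nmol/L. This agrees with 10% of the expected rise, 1.5 × exp[(0.4² + 0.25² + 0.25²)/2] = 1.73.

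The last row shows a limit: an additive shift does not cancel exactly after taking logs, and the interaction rate rises to about 9%.

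**5. Passages that disagree.** {12} places the first acute measurement at Tr1. {7}, {11a}, {20a}, Table 2 and the section on stress system activity all say the second lesson, and no sample is scheduled at lesson 1. {9} puts all specimen analyses in one laboratory; {33} names two.

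**The case against.** A reader might infer that assay drift cannot be told apart from reduced stress reactivity. The documents do not support that. Reactivity is the change within a session, and the ANOVA in {20a} already contains the interaction that tests it. The three samples of a lesson share any lesson-level shift, so that term stays near 5% in most settings. The rates of 9% to 74% belong to the level main effect only.

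A reader might also take lesson and assay batch to be fully confounded. That goes beyond the text. {33} speaks of one time point; {11a} and the section on stress system activity use the term for T0, T1 and T2, and both lessons lie between T0 and T1. Assaying them together is not excluded. Each lesson also yields 56 × 3 = 168 samples, and recruitment ran from June 2020 and was still open at the July 2021 version. If several runs were needed per lesson, part of the run error would average out. For this reason the shift above is called a net shift, and its size is assumed.

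The quality control in {18a} limits drift, but passing it does not balance lessons across runs. Plate layout may be left to a laboratory manual; the schedule in {33}, however, is stated and points the wrong way.

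Sampling only the intervention group is an open design choice, since the control group has no cycling lesson to sample. That is fair. It limits what may be concluded and is not itself an error.

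**Conclusion.** The point holds in limited form. On the natural reading of {33} with Table 2, assay run largely coincides with lesson, and no control arm absorbs a shift. A comparison of cortisol levels between lessons 2 and 7 could then be falsely significant in about 9% to 74% of trials. This rests on 56 completers, a paired log SD of 0.4 to 0.6 and a net shift of 5% to 15%, none of which the protocol gives apart from the drop-out figure behind the 56.

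The reactivity contrast is largely protected: 4% for the additive shift on raw data, 5% to 11% for proportional shifts of 5% to 20% on raw data, and about 5% for a 15% proportional shift on log data. The planned comparison of arms at T0, T1 and T2 is not in question as long as both arms share the shift.

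What makes this worth changing is that {7} allows the exposed reading, {20a} does not choose between the terms, and a better schedule is available with the storage already planned. The Tr1 label and the laboratory wording need correcting in any case.

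**What to change.** - **{33}:** assay each participant's tr2 and tr7 samples in the same run and the same laboratory, and likewise the T0, T1 and T2 samples, using the −30 °C storage already planned for saliva. This also removes the remaining exposure of the log-scale interaction to an additive shift.
- **{20a} and {7}:** name the sample-time by training-number interaction on log cortisol as the test of the secondary hypothesis.
- **{11a}:** describe the tr2 to tr7 result as an uncontrolled change within the intervention group. Same-run assay removes drift but not habituation, season or session differences.
- **{12}:** correct Tr1 to the second lesson.
- **{9} and {33}:** reconcile the one laboratory with the two, stating where cortisol is measured.

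Cost: laboratory results arrive later, and a few sentences change. No extra assays are needed if this is settled before analysis; any samples already assayed would have to be run again from the retained material.
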